## Methods/design

We will conduct a two-armed cluster randomized, controlled superiority trial to evaluate the effects of the intervention on the motivation, performance, and retention of VHTs in Uganda’s Masindi District. The intervention comprises a recognition-based non-financial incentives package, designed in August 2021 in collaboration with local leadership from Masindi District; this process is described in further detail below.

### Study setting and participants

The study will be implemented in Uganda’s Masindi District (see Fig. 1). As of July 2021, Masindi District has nine sub-counties, 32 parishes, and 312 villages. Masindi is a predominantly rural district, with most of the population living far from the main roads. Around 30% of the population lives on less than $1 per day, per a 2012 estimate [19]. Compared to national averages, Masindi District has a higher maternal mortality rate (499 per 100,000 live births, as compared to 435 per 100,000) and a higher proportion of adolescent deliveries (24.8% compared to 20%) [20] compared to the national rates. Vaccination coverage is lower than the national average, with around 71.8% of children receiving the DPT3 vaccine on schedule, compared to 84% nationally [20]. The District also experiences a high prevalence of malnutrition and infectious and communicable diseases [20]. In 2020–2021, Masindi District was ranked 107th out of 136 districts per a composite index calculated by Uganda’s MoH which ranks districts from best to worst-performing, signifying poor health sector performance [21]. This index considers staffing levels; coverage (e.g., tuberculosis case notification rate, antenatal care 4th visit coverage, the proportion of deliveries in health facilities, etc.); quality of care (e.g., the proportion of maternal deaths that are reviewed, the proportion of perinatal deaths that are reviewed, etc.); community health services (e.g., community VHT quarterly reporting rate, the proportion of children under-five dewormed in last six months); and management (e.g., local government performance assessment score, supervision performance assessment and recognition strategy score) [21]. Per this index, the national average is 64.4%; Masindi District is at 57.3% [21], which indicates that Masindi District is in the lower 50th percentile of districts for critical health and sanitation parameters. Masindi District’s selection as the study site was guided by the poor coverage of maternal and child health outcomes, and the topographical diversity within the three distinct ecological zones, which allows for the assessment of the VHT program under a range of geographical conditions.

**Fig. 1 Fig1:**
[figure not shown]
Masindi District, Uganda (July 2021)

### Inclusion criteria

VHTs who are identified as active by the parish supervisors are eligible for enrollment in the study, following consent. As of 2020, there was an estimated 517 VHTs across 32 parishes in the district, with an average of 16.1 VHTs per parish. The study plans on recruiting all active VHTs.

### Randomization and blinding

The intervention will be randomized at the parish level. Parishes will be randomly assigned with equal probability to either the intervention or comparison group within each sub-county. All 32 parishes will be randomized. Randomization will be conducted by a biostatistician independent of the study team through random number generation using STATA [22]. The study team will be blinded from the process of allocation assignment. The random numbers will be generated uniformly, then ordered ranks will be generated separately with a rank order of 0 or 1. Rank 0 will be labeled the comparison parish and rank 1 will be labeled the intervention parish. Rank orders will then be randomly assigned to parishes. There will be 16 parishes/arm and approximately 259 VHTs in each arm.

The intervention will not be blinded to the study team as the study team is engaged in supporting the delivery of the intervention to support the Masindi district. The intervention will not be blinded to the participants as the intervention involves public recognition of high-performing VHTs.

### The intervention

The development of the intervention incentive package is guided by the insights gained through a prior study that used a discrete choice experiment to understand the incentive preferences of the CHWs in Uganda [17]. The study indicated that reliable transportation (such as bicycles) and recognition (through the use of branded uniforms and/or identification cards) were highly valued by the CHWs. CHWs were willing to accept a decrease in salary of Ush 31,240 (US $8.5) for identity badges and of Ush 85,300 (US $23) for branded uniforms to no form of identification [17].

To determine the intervention to be tested and the criteria for assessing performance, the study team met with 16 stakeholders in Masindi District in August 2021. The stakeholders included VHT/Parish Coordinators; Health Assistants, who supervise VHTs; Health Inspectors; District Health Educators; District Health Officer; Biostatistician; and representatives/focal persons for district quality improvement, district surveillance, HIV, and malaria programs. The results of the prior study were presented to the stakeholders, and based on considerations of the sustainability of the intervention and the ability of the local district to financially sustain the intervention, the proposed intervention was adapted for the context. These discussions resulted in the following recognition-based incentives package: (1) a certificate which includes the name of the VHT and language describing the VHTs’ exemplary performance; (2) a branded jacket that would identify the VHT as a high performer (see Fig. 2); and a (3) a public recognition of VHTs who have been actively serving their communities.

**Fig. 2 Fig2:**
[figure not shown]
The recognition-based incentives provided during the public ceremony to VHTs

All VHTs who have submitted their quarterly reporting forms (see Additional file 2) to the health facility will be considered for recognition. VHTs will be provided with regular reminders to submit quarterly reports to health facilities during VHT engagement activities (e.g., monthly VHT phone survey, health facility data abstraction). VHTs will be assigned to different strata based on the size of the rural/urban parishes (i.e., urban small, rural small, rural large) given the differences in the number of households and proximity of households. Finally, the top 10% of performers within each stratum will be publicly recognized. Performance of the VHTs will be assessed based on the following three indicators: the proportion of children under 5 years of age with up-to-date immunization, the proportion of sick children under 5 years of age the VHT has attended to, and the proportion of women who attended at least four antenatal care visits. These indicators were chosen as they are what VHTs record in and report from their registers and are likely to be achieved by VHTs. The denominators for each variable will be abstracted at the village level from the official population projection statistics provided by the Masindi District government, District Planner’s Office.

The public recognition ceremony will be convened on a quarterly basis, as the VHTs provide their activity reports on a quarterly basis. Representatives from the district will convene and lead the ceremony and all VHTs from the intervention parishes will be invited. For the comparison parishes, it will be standard practice, where VHTs continue to provide services as usual; there will be no public recognition ceremony for VHTs who are from the comparison parishes. Any changes to the intervention, if needed, will be made based on the input from the District; changes will be made at the intervention (status of randomization) level, and not at the VHT level, and will be documented for better contextual understanding. Intervention adherence will be facilitated by regular reminders to VHTs to submit quarterly reports to health facilities during VHT engagement activities (e.g., monthly VHT phone survey, health facility data abstraction).

### Primary and secondary study outcomes

This study utilizes a mixed-methods approach to understand the impact of the intervention on the primary and secondary outcomes. The primary outcome of this study is changes in VHT performance (defined as the total number of home visits in the past three months). VHT performance is challenging to assess accurately as often VHTs may not have the tools to record their visits (e.g., registers), may not have received training to correctly record the information, and may not maintain records to accurately recall their activities. Therefore, VHT performance data will be collected in three specific ways: (1) through VHT surveys conducted at baseline and endline; (2) through the abstraction of quarterly reported data submitted to health facilities as VHTs are expected to report quarterly; and (3) through monthly phone surveys. Secondary outcomes for this study include the following: (i) VHT motivation (assessed using the validated Close-to-Close (CTC) Provider Motivational Indicator Scale [23]); (ii) VHT retention (measured through monthly self-reports); (iii) the other VHT performance measured by trends in service delivery; and (iv) trends in adoption of sanitary practices in each village. See Table 1 for the list of primary and secondary outcomes and the related data collection activities to measure them.

**Table 1 Tab1:** Primary and secondary outcomes and related data collection activities

	**Data collection activity**
**Primary outcome**	
** 1. VHT performance** *No. of total home visits in the last 3 months*	VHT survey VHT phone survey Abstraction from health facility report
**Secondary outcomes**	
** 2. VHT motivation** *Measured through the CTC Provider Motivational Scale. This scale has four sub-modules on work satisfaction, organizational commitment, community commitment, and work conscientiousness*	VHT survey
** 3. VHT retention** *Assessed through the proportion of leaving VHTs*	VHT phone survey
** 4. Other VHT performance (trends in service delivery)** *No. of visits for antenatal care* *No. of visits for postnatal care* *No. of visits to support immunization of children* *No. of referrals made to health facility* *No. of sick under-5 children attended by a VHT* *No. of people provided with HIV counseling* *No. of people provided with TB counseling* *No. of people provided with general counseling*	VHT survey VHT phone survey Abstraction from health facility report
** 5. Trends in adoption of sanitary practices per village** *No. of households with latrines* *No. of households with improved latrines* *No. of households with handwashing facilities* *No. of households with safe drinking water* *No. of households that are open defecation free*	VHT survey Abstraction from health facility report

### VHT recruitment and mobilization

The study team is working with the District to implement this study. Initial meetings were held to orient the District leadership to the study concept and study team. District leadership comprised the District Health Officers (DHO), District Focal Person for Community Health Activities, and the Biostatistician. The District Focal Person provided the study team with an orientation on VHT activities and responsibilities, as well as a list of currently active VHTs and Parish Coordinators. The study team will utilize this list to reach out to VHTs for recruitment and consent.

### Training data collectors

A 3-day training will be held to orient data collectors to the study and provide them with training on the study tools, human subjects research and ethics, and the consenting process. The third day of training will focus on using Open Data Kit (ODK) [24], a tablet-based data collection platform, and on pretesting the survey tool. All data collectors will have received a Bachelor’s degree and have fluency in Runyoro, Lugbara, and/or Kiswahili—the prevalent local languages in the study district.

### Data collection and timeline

Trained data collectors will implement the data collection activities. See Fig. 3 for the timeline of the intervention and data collection activities. To ensure participant retention for these data collection activities, the study team will provide regular reminders, which will occur via direct phone calls tied to upcoming data collection activity and at the quarterly recognition ceremonies.

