### Analysis plan

To assess the impact on the primary outcome (i.e., total household visits made per VHT), we will use Generalized Estimating Equations (GEE) to perform a linear regression analysis, adjusting for cluster effects at the parish level. A linear regression model assumes a normal distribution of the outcome: the number of household visits per VHT. If the data suggests that the outcome is not normally distributed, we will consider other model specifications such as the ordinal logit regression. The same approach will be taken for secondary outcomes to assess the estimated effects of the intervention. Intention-to-treat (ITT) with sensitivity analysis will be used to address protocol non-adherence. To clarify the ITT analysis approach, we plan to include all VHTs based on their allocation assignment at baseline data collection; however, if there are changes among VHTs in regard to their parish (i.e., if a VHT was initially in a comparison parish and has moved to an intervention parish during the duration of the study), we will monitor the percentage of VHTs that have crossed over (comparison to intervention parish and vice versa) and conduct sensitivity analyses to determine how to best proceed in regard to their inclusion in the analysis. We will document missingness patterns by intervention status to assess for random missingness. Depending on the type of missingness, we will consider strategies such as imputing or discarding the data. However, we do not expect the pattern to vary across the intervention and comparison arms.

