## Discussion

This study evaluates the impact of a public recognition intervention on VHT motivation, performance, and retention in Uganda. Given the limited financial support for the VHT program, the intervention was designed—through stakeholder engagement—with an emphasis on incentives that can be sustained beyond the context of this study and that are relatively inexpensive to administer. The intention of this study is not to suggest possible alternatives to financial compensation, but rather, additions to financial compensation that can be sustained locally.

As this study is being implemented during the ongoing COVID-19 pandemic, various COVID-19-related service disruptions may occur during the study. We expect that regular contact with the VHTs via phone calls will enable the research team to monitor these disruptions and account for them in the analyses and interpretation of the study results. The study predominantly relies upon VHT self-reporting data, which are subject to reporting and desirability bias; we plan on triangulating the data from multiple sources. There may be intervention spillover between the intervention and comparison parishes; however, VHTs in the comparison parishes will not be eligible for public recognition. This may lead to VHTs in the comparison parishes having lowered job satisfaction or motivation given that they are ineligible for the intervention. Lastly, incentives such as social recognition take time to register and require time to see corresponding improvements as a result of the incentives. Our study period is 12 months, which allows for four rounds of incentives to be delivered; this may be insufficient in capturing the longer-term effect of the intervention.

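### Data-collection reminders are also given at recognition ceremonies to which only intervention-parish VHTs are invited, so up to four extra response prompts exist in one arm only

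*Protocol article*

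**What the plan says.** Under Data collection and timeline, the protocol article states the purpose of the reminders: "To ensure participant retention for these data collection activities, the study team will provide regular reminders". It names two channels: the reminders occur "via direct phone calls tied to upcoming data collection activity and at the quarterly recognition ceremonies".

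Under The intervention, "all VHTs from the intervention parishes will be invited" to the ceremony, and "there will be no public recognition ceremony for VHTs who are from the comparison parishes". The Discussion gives the number of rounds: "Our study period is 12 months, which allows for four rounds of incentives to be delivered".

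A separate set of reminders concerns the quarterly reports: "VHTs will be provided with regular reminders to submit quarterly reports to health facilities during VHT engagement activities". These are described under The intervention, but they are attached to the phone survey and the facility abstraction, and no arm restriction is stated.

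On missing data, the Analysis plan will document missingness by intervention status and consider imputing or discarding, and adds that "we do not expect the pattern to vary across the intervention and comparison arms". The power section uses a single 90% response rate for both arms.

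**The concern.** Randomisation protects the comparison as long as outcomes are sought with the same effort in both arms. Here one of the two stated retention channels exists in one arm only, and no matching contact is described for the other. The ceremony belongs to the intervention. A reminder to complete a survey or answer a call does not, and it could be dropped without altering the certificate, the jacket or the recognition.

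The setting makes this more than a formality. Neither the study team nor the participants are blinded, and the Discussion concedes that "The study predominantly relies upon VHT self-reporting data, which are subject to reporting and desirability bias". Table 1 measures retention through the phone survey alone. That survey covers only VHTs who have a phone. For a VHT who cannot be called directly, the ceremony is the only other reminder channel named, and it is open only in intervention parishes.

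If the extra prompts change who responds in the intervention arm, the primary contrast mixes the incentive effect with a difference in who is measured. If they bring in less active VHTs, a real benefit is partly masked. If they bring in more engaged VHTs, a benefit is overstated. They also give a reason to doubt the expectation that missingness will be alike in the two arms.

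**Working it through.** **Channels by arm**

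| Prompt to take part in data collection | Intervention | Comparison |
|---|---|---|
| Direct phone calls (Data collection and timeline) | yes | yes, no arm restriction stated |
| Reminder at quarterly ceremony | up to 4 in 12 months | none |

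**The plan's own figure.** Inputs from Power estimation and sample size: 16 parishes and 240 VHTs per arm, 15 responding VHTs per parish, SD 25, intra-class correlation 0.2, two-sided 0.05, power 0.8.

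- Design effect = 1 + (15 − 1) × 0.2 = 3.8
- SE of the arm difference = 25 × √(2 × 3.8 / 240) = 4.45 visits
- Detectable difference = (1.96 + 0.84) × 4.45 = 12.46, against the stated 12.5; power at 12.5 is 0.802

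The figure reproduces, and this point does not challenge it.

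**Illustration of a shift.** The document gives no response by arm, so the response rates and gaps below are assumptions. Suppose VHTs who would respond in either arm have the same mean, and the prompts add responders in the intervention arm whose visits differ from that mean by D. Then

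shift = D × (r_int − r_comp) / r_int,

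power at 12.5 = Φ((12.5 + shift)/4.45 − 1.96), and the rejection rate with no true effect = Φ(−1.96 + |shift|/4.45) + Φ(−1.96 − |shift|/4.45). The SE is held at 4.45 throughout.

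| Assumed case | Shift (visits) | In SEs | Power at 12.5 | Rejection rate, no true effect |
|---|---|---|---|---|
| 95% vs 90%, D = −10 | 0.05/0.95 × (−10) = −0.53 | 0.12 | 0.768 | 0.052 |
| 95% vs 85%, D = −20 | 0.10/0.95 × (−20) = −2.11 | 0.47 | 0.647 | 0.076 |

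With D of the opposite sign the shift favours the intervention, and the two-sided rejection rate under no effect is the same. As a share of 12.5 visits, the two shifts are 0.53/12.5 = 4% and 2.11/12.5 = 17%. With equal response and equal make-up of responders, the shift is zero.

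The calculation treats the outcome as a level at endline. It takes no credit for baseline data.

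**The case against.** The case for leaving this alone has several parts.

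- **The extra effort is incremental.** Phone reminders carry no arm restriction. The phone survey makes at least three attempts a month and goes through the Parish Coordinator when a number is no longer active. This stands. It makes a large response gap less plausible but does not remove the asymmetry.
- **Invited is not the same as attending.** The document gives no attendance, so the number of prompts actually received is unknown. This stands, and it is why the point says up to four prompts are available and not that four are delivered.
- **The less favourable case is strong.** A 10-point response gap caused by an added reminder, with a 20-visit deficit (20/25 = 0.8 SD), has no support in the document. This stands.
- **The analysis may absorb some of it.** The primary outcome is defined as a change in performance, and a difference-in-differences analysis is planned. If the extra responders are equally far below the rest at baseline and endline, and the same VHTs are compared, that gap cancels. Imputation using baseline performance could also help. This stands in part: the GEE regression is named first, and imputation is only to be considered.
- **Retention has a cross-check.** The VHT listing at baseline, six months and endline is compiled with the VHT coordinator and facility in charge and does not depend on a VHT answering a call. This stands, although Table 1 names only the phone survey for retention.
- **Recognition itself may raise engagement with data collection.** Equal reminders would not remove that. True, but it is a consequence of the intervention, whereas the reminder is a procedure the team can choose.

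None of these explains why a measurement prompt should be placed where only one arm can receive it.

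**Conclusion.** The protocol article itself fixes the asymmetry; it is not a detail left for an analysis plan. One of the two reminder channels is open to intervention-parish VHTs only, on up to four occasions. This is an avoidable source of differential response, and it sits badly with the expectation of equal missingness.

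Its size and sign are unknown. Under the assumptions shown, the shift runs from about 0.5 visits (0.12 SE) to about 2 visits (0.47 SE), in either direction.

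Three stronger readings are tempting and are not supported:

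- *That the primary result will be biased, with power near 65% or a false-positive rate near 7.6%.* Those figures follow only from the assumed 95% vs 85% response and 20-visit gap. They illustrate; they are not a likely effect.
- *That follow-up effort is shown to differ in practice.* The document shows an invitation and a channel, not attendance or response.
- *That nothing done later about missing data can help.* The missingness review, the difference-in-differences analysis and the VHT listing may reveal or reduce the effect. They do not prevent it.

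The point is a cheap improvement to procedure and not a threat to the design.

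**What to change.** In Data collection and timeline, delete the ceremony as a reminder channel. State that data-collection reminders use the same channel, script, timing and number of attempts in both arms. If an in-person reminder is wanted, place it at a contact common to both arms, such as the quarterly facility abstraction, which The intervention section already counts among VHT engagement activities.

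The protocol is dated 17 November 2022 and recruitment began in August 2021, so some ceremonies may already have taken place. For those rounds, report the reminders delivered and the response to each data collection activity by arm, and read the planned missingness review in that light.

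The cost is one sentence of procedure and a short table. The downside is a possible small loss of response in the intervention arm.
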